## Abstract

**Simple Summary:**

Although comprehensive genomic profiling (CGP) has attracted attention in unresectable pancreatic cancer with metastasis, the success rate of CGP in specimens obtained by endoscopic ultrasound-guided tissue acquisition (EUS–TA) is not high. This study is expected to improve the success rate of CGP of unresectable pancreatic cancer with metastasis in the future by clarifying whether the optimal target of EUS–TA is primary or metastatic lesions.

**Abstract:**

EUS–TA in unresectable pancreatic cancer requires not only a tissue diagnosis but also tissue collection in anticipation of comprehensive genomic profiling. However, the optimal puncture target remains controversial. Therefore, the Primary and Metastatic Lesions in Pancreatic Cancer (PRIMATE) study was designed to clarify the optimal target by comparing the success rates for meeting OncoGuide NCC Oncopanel (NOP) analysis criteria on pre-check primary and metastatic lesion specimens obtained during the same EUS–TA session in patients with invasive pancreatic ductal adenocarcinoma. In this ongoing prospective study, two specimens, each from primary and metastatic lesions, are obtained by EUS–TA (typically using a 19G fine-needle biopsy needle) in patients with invasive pancreatic ductal adenocarcinoma. The primary endpoint is the proportion of EUS–TA specimens that meet NOP analysis criteria during pre-check (i.e., tumor cellularity of ≥20% and a tissue area of ≥4 mm^2^), which are then compared between primary and metastatic lesions. This study has been approved by the National Cancer Center Institutional Review Board (Research No. 2022-168). The results of this study will be reported at an international conference and published in an international peer-reviewed journal. The trial registration number is UMIN 000048966.

## 1. Introduction

In recent years, cancer genomic medicine has been implemented in clinical practice, and comprehensive genomic profiling (CGP) using next-generation sequencers (NGSs), which can detect a large number of gene sequences in tumor tissue specimens, has become available [1,2,3,4,5,6,7,8,9,10,11]. In pancreatic cancer, CGP has made it possible to select treatment options, such as molecularly targeted drugs and immune checkpoint inhibitors, that are suited to the patient, with new treatment options expected in the future [12,13,14,15,16,17,18,19,20,21]. Therefore, endoscopic ultrasound-guided tissue acquisition (EUS–TA) in unresectable pancreatic cancer requires not only a tissue diagnosis but also tissue collection in anticipation of CGP [22].

CGP systems currently approved in Japan include the OncoGuide NCC Oncopanel System (NOP; Sysmex Corporation, Hyogo, Japan) and Foundation One CDx Cancer Genome Profile (Fone; Foundation Medicine, Cambridge, MA, USA). The specimen criteria for the NOP system are tumor cellularity of ≥20% and a tissue area of ≥4 mm^2^, and that for the Fone system are tumor cellularity of ≥20% and a tissue area of ≥25 mm^2^ (Table 1).

In clinical settings, a pathologist evaluates the quality of the tissue specimen obtained by EUS–TA (during pre-check), and only cases that meet the criteria are subjected to CGP analysis (Figure 1). As pancreatic cancer is representative of low-cellularity tumors with abundant stromal components, the tumor cell content is reported to be 5–20%; accordingly, a greater amount of adequate tissue for CGP is required [23].

Two prospective studies have examined the proportion of successful CGP analyses of pancreatic tumor specimens. Carrera et al. reported a success rate of 97% (32/33) for CGP using NGS of cryopreserved tissue samples obtained by fine-needle biopsy (FNB) with a 22G needle [24]. Hisada et al. analyzed the pre-check results of EUS–TA specimens obtained by EUS–FNB with a 19G needle from a single lesion in patients with unresectable pancreatic cancer with metastasis (UR–M) and found that 63.6% (21/33) of specimens met NOP criteria [25]. Additionally, several retrospective studies have examined the success rate of genomic analysis of the pancreatic cancer specimens obtained using an FNB needle [24,26,27,28,29,30], including two analyses that focused exclusively on invasive pancreatic ductal carcinoma. Elhanafi et al. performed a retrospective study of EUS–TA in 167 patients with pancreatic cancer and found that 70.1% of specimens met NGS analysis criteria [29]. However, this study utilized a low threshold in the criterion for tumor cellularity (≥10%) in the pre-check. Park et al. performed a retrospective study of 190 patients with invasive pancreatic ductal adenocarcinoma and reported an NGS analysis success rate of 57.4% [30]. However, this study utilized a lower threshold for DNA content (≥50 ng) than that required for the NOP system. Thus, the reported percentages of specimens meeting NGS analysis criteria show considerable variation (57.4–100%), likely because of differences in outcome measures (percentage of successful analyses rather than that of the pre-check), specimen preservation methods, patient population (invasive pancreatic ductal adenocarcinoma with or without other cancer types), and specimen criteria (unspecified or lower criteria than that required for the NOP system).

The relationship between the EUS–TA technique and the percentage of successful CGP analyses has also been evaluated. Park et al. reported that the puncture needle diameter (22G or 19G) and tumor site (body–tail), but not needle type (fine needle aspiration or FNB), contributed to a successful CGP analysis of primary pancreatic specimens collected using EUS–TA [30]. Larson et al. reported that large FNB needle diameter (19G, *n* = 2; 22G, *n* = 41; and 25G, *n* = 2) was associated with a high success rate for meeting NGS analysis criteria (*p* = 0.05) [28]. Therefore, when performing EUS–TA with an FNB needle for CGP, a large puncture needle diameter, with a large amount of tissue sampled, is recommended to achieve a high analysis success rate.

However, the optimal puncture target remains controversial. Larson et al. compared the proportion of specimens that met CGP criteria between those obtained by EUS–TA for primary pancreatic lesions or percutaneous biopsies for metastatic lesions and found a significantly higher success rate for metastatic lesions than for primary lesions, despite the difference in sampling modalities (*p* = 0.036) [28]. Ikeda et al. reported that, overall, 39.2% (60/153) of pancreatic specimens obtained with an FNB needle met NOP analysis criteria during pre-check; however, primary lesion specimens (37.1%, 53/143) were significantly less likely than metastatic lesion specimens (70%, 7/10) to meet analysis criteria (*p* = 0.049) [31]. Nevertheless, data on the proportion of metastatic lesion specimens that meet CGP analysis criteria remain insufficient, and it is not yet clear whether primary or metastatic lesions have a high success rate for CGP analysis of invasive pancreatic adenocarcinoma.

Therefore, we designed a study to clarify the appropriate target for EUS–TA when CGP is planned for pancreatic ductal adenocarcinoma by comparing the success rates for meeting NOP analysis criteria between primary and metastatic lesion specimens obtained during the same EUS–TA session in patients with invasive pancreatic ductal adenocarcinoma. The protocols are described herein.

## 2. Study Design

### 2.1. Patients, Ethics, and Results Dissemination

The study was approved by the National Cancer Center Institutional Review Board (Research No. 2022-168). Protocol version 1.2 was finally approved on 23 May 2023. A summary of the study, its progress, and main results will be made available in the clinical registry system of the University Hospital Medical Information Network (UMIN ID: 000048966). The results will be reported at an international conference and published in an international peer-reviewed journal. All patients will be briefed on the study, and informed consent will be obtained before enrollment.

### 2.2. Study Design

This is an ongoing single-center prospective self-controlled trial. The study flowchart is shown in Figure 2.

### 2.3. Endpoints

The primary endpoint is the proportion of EUS–TA specimens obtained from primary and metastatic lesions that meet NOP analysis criteria. Although the NOP product catalog indicates tumor cellularity of ≥20% and a tissue area of ≥16 mm^2^, in actual clinical practice, a tissue area of ≥4 mm^2^ provides adequate DNA content (≥200 ng) for analysis. Thus, specimens with tumor cellularity of ≥20% and a tissue area of ≥4 mm^2^ are considered to meet NOP analysis criteria.

The secondary endpoints are as follows: rate of patients with primary or metastatic lesion specimens that meet NOP analysis criteria; technical success rates of EUS–TA with a TopGain 19G needle in primary and metastatic lesions; technical success rates of EUS–TA (regardless of needle type) in primary and metastatic lesions; adverse event rate, details, and severity; sensitivity, specificity, and accuracy of the histological differentiation of malignant and benign lesions in primary or metastatic lesion specimens; rates of successful NOP analysis of primary and metastatic lesion specimens; rate of patients who receive a drug targeting detected genetic mutations; details of genetic mutations detected upon NOP analysis; tumor cellularity and tissue area of all EUS–TA sessions; tumor cellularity and tissue area according to the nCounter system for all EUS–TA sessions; rate of patients who do not meet NOP criteria for both primary and metastatic lesion specimens and underwent liquid biopsy; rate of the necessity of percutaneous biopsy because specimens do not meet NOP analysis criteria for primary or metastatic lesions; and DNA amount in cases analyzed for DNA amount.

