### 2.6. Trial Examination Procedures

Participants undergo EUS performed by a physician who has performed at least 100 cases of EUS–TA as a primary physician. Pancreatic primary and metastatic lesions are characterized, and the maximum lesion diameter is measured in B-mode, followed by confirmation that there are no intervening vessels in the puncture route in Doppler mode. EUS–TA is typically performed using a TopGain 19G needle (SonoTip TopGain; Medi-Globe, Achenmuhle, Germany). Negative pressure is applied using suction with a 20 mL syringe or the slow-pull method, and approximately 20 actuations per pass are performed. If possible, the fanning technique is performed during actuation, but it is not mandatory. When a lesion cannot be identified or the puncture line is technically difficult, a change in the puncture needle or physician is considered. If the puncture remains difficult, it is not forced, and the patient is considered a technical failure. If both primary and metastatic lesions are difficult to puncture, alternative biopsies, such as percutaneous biopsies, are considered. Changing the puncture needle for each lesion is not mandatory, but if the needle deteriorates, it is acceptable to use a new needle as needed. It is not specified whether primary or metastatic lesions should be punctured first, but the puncture is basically performed alternately on the primary and metastatic lesions.

For both primary and metastatic lesions, obtained specimens are placed in shale, and a portion of the specimen is cut and considered for rapid on-site evaluation (ROSE). However, ROSE is not mandatory. When ROSE is performed, the remaining specimens are not included in the study because of the small number of specimens. If malignant cells are not confirmed by ROSE, changes in the puncture site, target, and needle are considered; however, a diagnosis of malignancy may be made by histological examination in some cases. Therefore, even if malignant cells cannot be confirmed using ROSE, additional puncturing, without changing the site or puncture method, is considered acceptable. All collected specimens, including residual specimens after ROSE, are individually preserved in formalin bottles for histological evaluation.

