The procedure is terminated once two specimens each are obtained from primary and metastatic lesions, after confirming by EUS and endoscopy that there are no findings suggestive of hemorrhage. If bleeding is suspected, endoscopic hemostasis or endovascular treatment will be considered.

Specimens obtained by EUS–TA are thinly sliced after formalin fixation and stained with hematoxylin and eosin. Specimens, excluding those from the ROSE session, are checked to determine whether they meet NOP analysis criteria. The sample volume required for NOP analysis is five 10 μm thick sections, with tumor cellularity of ≥20% and total DNA content of ≥200 ng per slide. A tissue area of approximately 16 mm^2^ per slide is recommended; however, a tissue area of 4 mm^2^ or more yields > 200 ng of total DNA. Therefore, we consider specimens with tumor cellularity of ≥20% and a tissue area of ≥4 mm^2^ as successfully meeting NOP analysis criteria. The pathological evaluation is performed by two pathologists, and any discrepancies in the measurements are resolved by discussion. In this evaluation, tumor cellularity is evaluated at five levels (>80%, 60–80%, 40–60%, 20–40%, and <20%), and tissue area is evaluated at four levels (≥25, 16–25, 4–16, and <4 mm^2^).

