### 2.7. Sample Size Determination and Statistical Analysis

The proportion of metastatic lesion specimens that meet NOP analysis criteria is expected to be approximately 70%. The proportion of primary lesions that meet NOP analysis criteria is likely to be lower than the 63.6% reported by Hisada et al. because of the reduced number of passes in the PRIMATE study. In addition, in our previous retrospective study, the proportion of primary tumor specimens obtained by EUS–TA with a 19G needle meeting criteria on pre-check was 53.8%, with a median number of punctures of four. Therefore, the proportion of primary lesion specimens that meet NOP analysis criteria in the present study is expected to be approximately 45%. Accordingly, the minimum sample size required for a Fisher’s exact test is 56 patients, assuming a one-sided significance level of 0.05 and a power of 80%. Assuming that approximately 10% of registered patients will experience difficulty in puncturing, a sample size of 61 patients is planned.

The proportion of EUS–TA specimens meeting NOP analysis criteria will be compared between primary and metastatic lesions using Fisher’s exact test. Statistical significance is set at *p* < 0.05.

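### The primary endpoint and Fisher's test are worded per specimen, with two specimens per lesion, but the 56 patients reproduce only with one result per lesion

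*Protocol article*

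**What the plan says.** All references are to the protocol article.

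- **Endpoint (Section 2.3):** "The primary endpoint is the proportion of EUS–TA specimens obtained from primary and metastatic lesions that meet NOP analysis criteria". A rate of patients is listed separately among the secondary endpoints.
- **Sampling (Section 2.6):** "The procedure is terminated once two specimens each are obtained from primary and metastatic lesions". Collected specimens "are individually preserved in formalin bottles for histological evaluation". No sentence says whether a lesion's two specimens are counted separately, combined, or scored as a success when either one qualifies.
- **Design (Section 2.2):** "This is an ongoing single-center prospective self-controlled trial".
- **Planning rates (Section 2.7):** "The proportion of metastatic lesion specimens that meet NOP analysis criteria is expected to be approximately 70" per cent, and "the proportion of primary lesion specimens that meet NOP analysis criteria in the present study is expected to be approximately 45" per cent. The second figure is argued down from 63.6% in a cited prospective 19G study, because fewer passes are made here, and from the group's own retrospective rate, which "was 53.8%, with a median number of punctures of four".
- **Sample size and test (Section 2.7):** "the minimum sample size required for a Fisher’s exact test is 56 patients", at one-sided 0.05 and 80% power, with 61 planned. The primary comparison is Fisher's exact test on the proportion of specimens.

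**The concern.** The endpoint and test count specimens, while the sample size counts patients. With two specimens per lesion these units differ by a factor of two, and they define different quantities: a rate per specimen is not the rate at which a lesion yields usable tissue.

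Two things are at stake. First, the result can be computed in more than one way from the same data, and the article does not settle which way is primary. Second, if the stated rule is followed literally, Fisher's test ignores two dependences. Two passes into one lesion share its cellularity and stroma, and the primary and metastatic lesions belong to the same patient. The test then has no controlled error rate, in a study meant to change the recommended puncture target.

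**Working it through.** **1. Reproduce the 56.** Inputs from Section 2.7: rates 0.45 and 0.70, one-sided alpha 0.05, power 0.80. Exact power is the sum, over all outcome pairs that Fisher's test rejects, of Bin(x₁; n, 0.45) × Bin(x₂; n, 0.70).

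| Results per lesion type | Exact one-sided Fisher power |
|---|---|
| 54 | 0.792 |
| 55 | 0.803 |
| 56 | 0.814 |
| 112 (two specimens × 56, all independent) | 0.979 |

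The stated 56 is thus a number per lesion type with one result per lesion. If the unit were the specimen, 56 per lesion type would need only 56/2 = 28 patients.

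**2. Type I error if specimens are pooled.** Let ρ be the correlation between two specimens of one lesion, and τ the correlation between a primary and a metastatic specimen of one patient. With N patients and a common rate p:

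- True variance of the difference: [p(1−p)/N] × (1 + ρ − 2τ)
- Variance if all 2N + 2N specimens were independent: p(1−p)/N
- Ratio: 1 + ρ − 2τ

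So ρ inflates the error and τ deflates it. Simulation results for pooled one-sided Fisher follow (N = 56, p = 0.575, the midpoint of 0.45 and 0.70; 40,000 runs per cell). All correlations and the common rate are assumptions.

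| ρ | τ = 0 | τ = 0.2 | τ = 0.4 |
|---|---|---|---|
| 0 | 0.037 | – | – |
| 0.3 | 0.055 | 0.028 | – |
| 0.5 | 0.073 | 0.043 | 0.017 |
| 0.7 | 0.082 | 0.058 | 0.030 |
| 0.9 | 0.097 | 0.072 | 0.043 |

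Cells with the same ratio agree: at ratio 1.5, (0.5, 0) gives 0.073 and (0.9, 0.2) gives 0.072. Fisher's own conservatism explains the 0.037 at zero correlation. The effective number per lesion type, 112/(1+ρ), is 86, 75, 66 and 59 for ρ = 0.3, 0.5, 0.7 and 0.9.

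**3. How far the two units differ.** Under an at-least-one-of-two rule, the lesion rate is 1 − [(1−p)² + ρp(1−p)].

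- p = 0.45, ρ = 0: 1 − 0.3025 = 0.698. With ρ = 0.5: 1 − (0.3025 + 0.1238) = 0.574.
- p = 0.70, ρ = 0: 1 − 0.09 = 0.910. With ρ = 0.5: 1 − (0.09 + 0.105) = 0.805.

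If the planning rates were per specimen, Fisher power at 56 lesions per type under this rule would be 0.855 (ρ = 0) or 0.798 (ρ = 0.5). The rates reported would change far more than the power.

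**4. Does a paired lesion-level test fit 56 patients?** Take 0.45 and 0.70 as lesion rates. With independent lesions the discordant probability is 0.55 × 0.70 + 0.45 × 0.30 = 0.385 + 0.135 = 0.52. Exact one-sided McNemar power, summed over the number of discordant pairs, is 0.81 at 56 pairs. With τ = 0.2 and 0.4 between a patient's two lesions, the discordant probability falls to 0.43 and 0.34, and power rises to 0.88 and 0.96.

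**The case against.** The strongest reply is that no pooled analysis is intended. The Introduction describes 21/33 as a proportion of specimens for a study of a single lesion per patient, so the article uses the word loosely. The 56 itself points to one result per lesion. No denominator of 112 appears anywhere, and specimens from ROSE sessions are left out of the criteria check, so exactly two evaluable specimens per lesion are not assured. A combining rule may also sit in the full protocol, which is not shown.

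Much of this stands. A reader might infer that the trial will pool 112 against 112 specimens and so inflate its type I error. The documents do not support that: pooling is the literal reading but not a shown intention, and the error can fall below 0.05 as easily as rise above it. A reader might also infer that both planning rates are per lesion. The reduction for fewer passes makes sense as a per-lesion argument for the 45%, since fewer passes do not in themselves lower the yield of each specimen. The 70% carries no pass count and no such adjustment, so its unit is not shown.

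What does not stand is that this is mere condensed detail. The article itself states the endpoint, the test, the specimens per lesion and the sample size, and these do not share a unit. It also separates a rate of patients from the specimen rate.

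**Conclusion.** The point holds as a mismatch between the stated endpoint and test (per specimen) and the stated sample size (one result per lesion per patient). That part rests only on figures in Section 2.7: power 0.81 at 56 vs 56, against 0.98 at 112 vs 112 if independent.

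The consequence for error control is conditional. If the wording is followed literally, one-sided type I error is roughly 0.02 to 0.10 over the assumed correlations, with no fixed direction. Even with one result per lesion, Fisher's test would still ignore the self-controlled pairing. This should be settled before analysis, because the primary result and the validity of its only test both depend on it.

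**What to change.** Before the data are analysed:

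1. Make the lesion the unit of the primary endpoint, with one pre-specified rule for combining its two study specimens. One example is success if at least one of them meets both thresholds already in Section 2.3 (tumor cellularity ≥20% and tissue area ≥4 mm²). Other rules are possible; what matters is that one is fixed.
2. Analyse the resulting one pair per patient with a paired test (exact McNemar).
3. State that the 70%, the 45% and the 56 refer to that unit, and give the basis for the 70% in that unit.
4. Report any specimen-level proportion as secondary, using a GEE or mixed logistic model that allows for clustering within lesion and patient.

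The cost is endpoint and analysis wording. If 45% and 70% hold per lesion, 56 evaluable pairs keep at least 80% power under the paired test for the non-negative correlations checked above. The article says specimens are preserved individually but not that each is scored separately. If they were not, some re-reading of stored material would be needed.

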### 2.4. Eligibility Criteria

Eligibility criteria are as follows: suspected invasive pancreatic ductal adenocarcinoma (or a confirmed diagnosis of invasive pancreatic ductal adenocarcinoma); metastatic lesions on pre-procedure imaging or prior EUS examination; aged older than 18 years; Class 0–2 on the Eastern Cooperative Oncology Group Performance Status scale; no gastrointestinal strictures in the pharynx or esophagus on pre-procedural imaging or prior endoscopy examination; pre-procedure imaging or EUS indicating that both primary and metastatic lesions can be safely punctured in EUS–TA with a 19G FNB needle, without interventions on blood vessels, other tumors, or other organs; no prior radiotherapy or chemotherapy for pancreatic cancer; able to withdraw from antithrombotic medication based on guideline criteria [32]; no specific bleeding risk (prothrombin time–international normalized ratio < 1.5 or platelet count > 50,000/L); and no more than a moderate volume of ascites (i.e., clear accumulation of ascites at the site of the possible puncture route for EUS–TA).

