### 2.5. Exclusion Criteria

The exclusion criteria are as follows: two or more lesions in the pancreas suspected of pancreatic cancer; psychosis or psychiatric symptoms that interfere with daily life and make study participation difficult; and enrollment in the study deemed as inappropriate by a physician.

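### The bleeding-risk entry criterion joins its INR and platelet limits with *or*, so read literally a patient who fails one of them is still eligible

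*Protocol article*

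**What the plan says.** Section 2.4 of the protocol article lists the conditions a patient must meet to enter. One of them is "no specific bleeding risk", followed by a bracket giving prothrombin time "international normalized ratio < 1.5 or platelet count > 50,000/L". The next condition, on ascites, also carries a bracket: "clear accumulation of ascites at the site of the possible puncture route for EUS–TA". That bracket describes what must be absent.

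The article contains other safeguards that bear on bleeding:

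- Section 2.4 asks for imaging or EUS evidence that "both primary and metastatic lesions can be safely punctured in EUS–TA with a 19G FNB needle", and that the patient is "able to withdraw from antithrombotic medication based on guideline criteria".
- Section 2.5 excludes patients with "enrollment in the study deemed as inappropriate by a physician".
- Section 2.6 requires "a physician who has performed at least 100 cases of EUS–TA as a primary physician" and "confirmation that there are no intervening vessels in the puncture route in Doppler mode". It also calls for a check for hemorrhage before the procedure ends, with hemostasis if bleeding is suspected.

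None of these states an INR or platelet value. Section 2.1 says that protocol version 1.2 is the approved version; that document is not shown.

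**The concern.** A patient is free of the two named risks only when neither is present. With limits written in the safe direction, that calls for *and*. The printed *or* makes one satisfactory result enough, so a markedly raised INR or a very low platelet count would not by itself make a patient ineligible.

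What is at stake is patient safety and whether eligibility can be checked as written. Under Section 2.6 each session aims for two specimens from each of two lesions, typically with a 19G needle and about 20 actuations per pass. As the rule stands, a patient failing one limit could be recorded as eligible on this criterion with no deviation noted. Adverse event rate and severity are secondary endpoints, so who may enter also bears on how those results are read.

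**Working it through.** The article gives no figure to reproduce here, so the check is one of logic.

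**Inputs (Section 2.4).** Let I stand for INR < 1.5 and P for platelet count > 50,000 in the printed unit. The criterion as a whole demands absence of bleeding risk.

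**Intended rule.** Risk is present if INR ≥ 1.5 or platelets ≤ 50,000, that is, (not I) or (not P). Its absence is the negation:

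not[(not I) or (not P)] = I and P.

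**Reading A: the bracket describes the safe state.** The printed rule is I or P.

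**Reading B: the bracket lists what must be absent**, as the ascites bracket does. The printed rule is then not(I or P) = (not I) and (not P), that is, INR ≥ 1.5 and platelets ≤ 50,000.

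| INR < 1.5 | Platelets > 50,000 | Intended: I and P | Reading A: I or P | Reading B: not(I or P) |
|---|---|---|---|---|
| met | met | eligible | eligible | not eligible |
| met | failed | not eligible | eligible | not eligible |
| failed | met | not eligible | eligible | not eligible |
| failed | failed | not eligible | not eligible | eligible |
| **Combinations admitted** | | **1 of 4** | **3 of 4** | **1 of 4 (the wrong one)** |

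The second row would cover, for illustration, an INR of 1.0 with platelets of 20,000; the third, an INR of 3.0 with platelets of 200,000. Three of the four combinations carry at least one risk (rows two to four), and Reading A admits two of those three. Reading B is absurd clinically and nobody would apply it. Its only use is to show that the alternative parse does not rescue the wording. The finding rests on Reading A.

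**Is the limit set correctly elsewhere?** No. The antithrombotic condition concerns stopping medication and defers to a guideline that is not shown; it does not address thrombocytopenia, or a raised INR from another cause. The safe-puncture condition concerns the lesions and the route to them. The physician's exclusion is discretionary. Operator experience and the Doppler check concern technique and anatomy. The hemorrhage check comes after the punctures.

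**Printed unit.** The platelet limit appears per litre. A micro sign may have been lost when the text was read from PDF, so this is something to confirm and carries no weight in the conclusion.

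**The case against.** The strongest reply is that the lead phrase is the rule and the bracket only explains it. A patient with an INR of 3.0 plainly has a bleeding risk, and clinicians would almost certainly apply *and*. The study is single-center, which limits inconsistent interpretation, and several other safeguards stand between a patient with poor coagulation and the needle. The slip may also exist only in the article, since enrolment runs under version 1.2. Finally, the comparison is within patients, so a looser bleeding criterion does not unbalance it. On this view the point is a wording correction with no demonstrated harm.

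Most of this stands. The intent is clear, practical harm is probably limited, no inferential quantity changes, and the article cannot show which word version 1.2 uses. The count of combinations describes the rule and says nothing about how many patients are affected.

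It does not remove the point. The article chose to give a numeric definition and gave one that contradicts the phrase it defines. That is an error in what is stated, not a detail left to the full protocol. Someone checking eligibility works from the numbers, and no other text in the article supplies the correct ones. A clear intent makes the correction easy; it is no reason to leave the text as it is.

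**Conclusion.** The concern holds. The only numeric coagulation limit in the article is wrong as written: it admits three of four INR/platelet combinations where one was evidently meant, including two in which a limit is failed. This is a drafting error in a safety criterion and should be corrected.

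The conclusion rests on the printed word *or* and on taking the lead phrase to mean that both limits were intended. It assumes nothing about how often either limit is failed. The article gives no such rates, so the number of patients affected cannot be estimated, and it may be small given the other safeguards. Whether any patient was exposed depends on version 1.2 and on practice at the site. Sample size, significance level and the primary comparison are unaffected.

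**What to change.** Reword the bracket in Section 2.4 as: prothrombin time–INR below 1.5 **and** platelet count above 50,000/µL, confirming the platelet unit at the same time. Then compare it with approved protocol version 1.2:

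- If version 1.2 already says *and*, correct the article only.
- If version 1.2 carries the same *or*, amend it and check the baseline INR and platelet count of every enrolled patient against the corrected rule. The study is described as ongoing, so the amendment would also protect later participants.

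The cost is one word, plus a review of baseline laboratory values in the second case only. Design, sample size and primary analysis stay as they are.
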